## Abstract

**Background:**

Childhood apraxia of speech (CAS) is a motor-based speech sound disorder (SSD) with a core impairment in the planning and programming of spatiotemporal parameters of speech movement sequences. CAS may cause deficits in both segmental and suprasegmental components of speech, and it can severely affect children’s ability to speak intelligibly and communicate effectively and impact their quality of life. Assessment tasks, such as the maximum performance tasks (MPT) and Syllable Repetition Task (SRT), examine children’s segmental sequencing skills to assist with the diagnosis of CAS. In Hong Kong, although the MPT and SRT have been used clinically to diagnose CAS in Cantonese-speaking children, their validity has not been reported. There is an urgent need for such investigations. Suprasegmentally, lexical stress errors have been reported as a consensual feature and to aid in the diagnosis of CAS. However, there are challenges in diagnosing CAS in children who speak tonal languages like Cantonese. A recent study has reported lexical tone errors in Cantonese-speaking children with CAS. Furthermore, deficits in pitch-variation skills were found in Cantonese-speaking children with CAS using a tone sequencing task (TST). It is hypothesized that there is a universal deficit in pitch-variation skills among tonal and nontonal language speakers with CAS. Further investigations of pitch-variation skills using the TST in Cantonese-speaking children with CAS may shed light on suprasegmental deficits in tonal languages and contribute to the development of a valid diagnostic tool for CAS in children who speak other tonal languages, such as Vietnamese, Thai, and Mandarin.

**Objective:**

This study aims to examine the diagnostic potential of the MPT, SRT, and TST in diagnosing Cantonese-speaking children with CAS and to investigate pitch-variation skills in Cantonese-speaking children with and without CAS.

**Methods:**

A total of 25 children with CAS and 3 groups of age- and gender-matched controls (non-CAS SSD only group, non-CAS SSD co-occurring with language impairment group, and typical development group) will be recruited. All participants will perform the MPT, SRT, and TST measures. Their performances on these tools will be perceptually judged and acoustically measured.

**Results:**

Data collection will last from January 1, 2022, to October 30, 2023. As of August 2022, the project has recruited 4 children in the CAS group, 21 children in the non-CAS SSD group, 4 children in the speech and language impairment group, and 53 children in the typical development group.

**Conclusions:**

It is anticipated that Cantonese-speaking children with CAS will have poorer pitch-variation skills than the control groups and that the MPT, SRT, and TST will be appropriate diagnostic tools for identifying CAS in Cantonese-speaking children. The project will benefit the field of speech-language pathology locally and internationally, with short- and long-term impacts.

**International Registered Report Identifier (IRRID):**

DERR1-10.2196/40465

## Introduction

### Background

Childhood apraxia of speech (CAS) is a motor-based speech sound disorder (SSD) with a core impairment in planning and programming of spatiotemporal parameters of speech movement sequences. It can occur as an idiopathic neurogenic SSD or as a result of known neurological impairment [1]. It can severely affect children’s ability to speak intelligibly and communicate effectively. CAS onsets from childhood and may persist into adolescence and adulthood [2-4]. If left untreated, the quality of life of children with CAS will be affected because of the long-term consequences of CAS on articulation, speech intelligibility, expressive language [5], academic performance, and social functioning [2-4,6,7].

CAS in children is characterized by deficits in both segmental and suprasegmental components of speech. The American Speech-Language-Hearing Association [1] reported that there are three consensual features, including (1) inconsistent errors in sequential repetitions; (2) deficits in coarticulation or syllable segregation (ie, choppy speech); and (3) prosodic deficits, especially lexical stress errors. Lexical stress errors, as one of the consensual features of CAS, have been widely studied in English speakers because of their high value as a suprasegmental marker of CAS [8]. The errors reflect underlying deficits in speech motor planning and programming skills that control the intensity, frequency, and duration of suprasegmental parameters. Deficits in the temporal control of lexical stress production have been documented, but it has been difficult to separate other specific acoustic aspects of lexical stress, such as pitch [9].

### CAS Diagnosis in English-Speaking Children

The gold standard for making a CAS diagnosis primarily relies on perceptual judgments of CAS experts. However, very recently, a pilot study reported only moderate agreement among 4 expert listeners [10]. Along with perceptual judgment, the maximum performance tasks (MPT) [11] and Syllable Repetition Task (SRT) [12] have been reported to provide valuable relevant information about segmental sequencing skills in children with CAS. Both MPT and SRT assess deficits in speech processing. The MPT aims to assess motor involvement in children with speech problems [11]. Specifically, the maximum repetition rate for trisyllabic stimuli (MRRtri) and maximum fricative duration (MFD) in MPT assess underlying deficits in the motor planning and programming of speech [13], while the maximum repetition rate for monosyllabic stimuli and maximum phonation duration assess deficits in speech motor execution. The SRT targets encoding, memory, and transcoding processes, which refer to mapping, prearticulatory or phonological planning, and transformation of the phonological plan into a motor plan, respectively [14]. Although the terminology is not identical, both the MPT and SRT address the same underlying deficits of CAS, speech motor planning and programming skills. Research has shown that the MPT has high sensitivity and specificity (ranging from 89% to 100%) in making a CAS diagnosis [11], whereas a cutoff transcoding score of 80 on the SRT is able to differentiate children with CAS from children with concomitant speech delay and language impairment (LI) [15].

### CAS Diagnosis in Cantonese-Speaking Children

There are challenges in diagnosing CAS in children who speak tonal languages like Cantonese. In Hong Kong, speech-language pathologists may apply English-based research findings to assess, diagnose, and treat children with CAS among the local Cantonese-speaking population. Although MPT and SRT have been used clinically to diagnose CAS in Cantonese-speaking children, the validity of applying these objective measures and diagnostic criteria from English-speaking populations to Cantonese-speaking populations is unknown. Owing to the segmental and suprasegmental differences between English and Cantonese, such as the fact that English has lexical stress patterns while Cantonese has lexical tones, English-based findings cannot be fully applied to Cantonese speakers with CAS, especially as prosodic deficits are one of the consensual clinical features of CAS. The current gold standard relies on expert perceptual judgment of clinical features reported in the English literature. Therefore, it is possible that misdiagnoses or underdiagnoses are occurring in the current clinical practice in Hong Kong. As higher frequency treatment is suggested for children with CAS [16] owing to the need for speech motor learning, inaccurate diagnoses may impact children, families, and society in terms of allocation of resources. Therefore, a valid diagnostic tool is urgently needed for Cantonese speakers with CAS to correctly identify and provide appropriate treatment to children with CAS.

### Previous Pilot Studies

A recent study [14] identified a new clinical feature, namely tone production errors, which has not been reported in English speakers with CAS. The authors proposed that the same underlying deficit of speech motor planning and programming skills manifests differently in Cantonese and English [14]. Both English and Cantonese speakers with CAS may have similar control challenges with the correct production of segments; however, they control suprasegmentals differently because of linguistic differences. Suprasegmentals are overlaid differently for lexical stress in English versus lexical tone in Cantonese. English speakers apply 3 stress features—simultaneous pitch, loudness, and duration variations—to syllables to express a grammatical or pragmatic meaning. Cantonese speakers vary the pitch of segments to indicate different lexical meanings. Owing to these differences, further investigations of lexical tone errors are vital to increase the understanding of tone production skills in children with CAS.

In an effort to further explore tone production skills in Cantonese-speaking children with CAS, tone sequencing tasks (TSTs) have been used in 2 studies to examine the accuracy, consistency, and duration of tone production in Cantonese-speaking children with CAS [17,18]. The TST is considered to be a potential assessment task that reflects impairment in speech motor planning and programming in Cantonese-speaking children with CAS [17,18]. It requires children to produce 5 repetitions of each item that is formed of 3 early-acquired Cantonese tones, that is, tone 1 (high-level), tone 2 (high-rising), and tone 4 (low-falling). Wong et al [18] administered the initial version of the TST to 2 Cantonese-speaking children with CAS and 2 Cantonese-speaking children with non-CAS SSDs. The results showed that children with CAS performed significantly more poorly than children without CAS in sequencing tones. The effect sizes (Cohen *d*) for tone accuracy and consistency were 0.68 and 0.60, respectively. Both of them were considered to be medium-to-large effect sizes.

In a subsequent study, the research team examined the linguistic effects of syllable structure and lexical status on TSTs using the second version of the TST [18]. A total of 4 Cantonese-speaking children with CAS were matched with 3 children with non-CAS speech and LI (S&LI), 3 with LI alone, and 3 with typical development (TD). Tone accuracy was judged perceptually and calculated as the percentage of tones correct. The consistency strength procedure adopted from the study by Williams et al [19] was used to calculate consistency scores. In the study by Wong et al [20], the team added 2 acoustic measures (ie, fundamental frequency [F0] values and acoustic duration) to further examine the data. The results showed both syllable structure and lexical status effects. Cantonese-speaking children with and without CAS showed significant between-group differences in F0 values for both vowel and consonant-vowel structures, as well as tone accuracy, tone consistency, and acoustic duration of word stimuli. A small to medium effect size (Cohen *d* ranging from 0.22 to 0.61) was obtained for F0 values, whereas large effect sizes were obtained for tone accuracy (Cohen *d* ranging from 1.37 to 1.98), tone consistency (Cohen *d* ranging from 1.36 to 1.85), and acoustic duration (Cohen *d* ranging from 0.9 to 1.45). The results suggest that syllable structure and lexical status play some roles in tone sequencing skills in children with CAS. In summary, these pilot studies suggest that children with CAS have difficulty with pitch-variation skills, specifically tone sequencing skills, and perform more poorly than control groups. The findings also support the diagnostic potential of TST as it provides a platform to investigate pitch variation in children with CAS and should be further developed as a linguistically appropriate assessment tool for Cantonese-speaking children. However, the generalizability of these findings is limited because of the extremely small sample sizes.

### Studying Pitch-Variation Skills Using the TST

Pitch-variation skills refer to the skills of varying F0 values within and between syllables in tonal languages. Pitch-variation skills present in English lexical stress patterns and Cantonese lexical tones. Although lexical stress errors have been empirically studied and it has been found that children with CAS have a deficit in the temporal control of lexical stress productions [9], the development and disorders of pitch-variation skills embedded in lexical stress errors remain unknown. Kopera and Grigos [9] attempted to examine the acoustic properties (ie, duration, peak F0, and average F0) of lexical stress errors using the pairwise variability index [21] between children with and without CAS. No significant between-group difference was found. The authors concluded that lexical stress errors in children with CAS can only be studied in a collective fashion, such as using the lexical stress ratio [8], which examines pitch, loudness, and duration simultaneously, instead of investigating acoustic parameters independently.

Nevertheless, new findings have shown significant between-group differences in both F0 values and acoustic duration between children with CAS and control groups [20]. This preliminary result suggests that Cantonese-speaking children with CAS have difficulty in varying pitch and that pitch-variation skills in Cantonese speakers with CAS can be studied independently via the TST in the context of this tonal language. This provides the basis for further investigations of pitch-variation skills in children with CAS who speak other tonal languages (eg, Mandarin, Vietnamese, and Thai) as well as children with CAS who speak nontonal languages (eg, English). TST can be used in English to assess pitch-variation skills in children with CAS in an out-of-stress context. This application may elucidate the role of pitch control in out-of-stress contexts and shed light on pitch control across languages in speakers with CAS.

### The Goal of the Proposed Study

This study aims the following:

To show that the MPT and SRT can contribute to the diagnosis of CAS in Cantonese-speaking children.To document differences in pitch-variation skills in Cantonese-speaking children with versus without CAS.To prove that TSTs are effective in diagnosing CAS in Cantonese-speaking children.

We hypothesized the following:

The MPT and SRT would differentiate Cantonese-speaking children with CAS from those without CAS.Cantonese-speaking children with CAS would have significantly poorer pitch-variation skills than the control groups.TSTs would differentiate Cantonese-speaking children with CAS from those without CAS.

## Methods

### Protocol Version

The original version of the protocol was submitted to the Research Grants Council of the Hong Kong Special Administrative Region Government on October 30, 2020. This protocol is version 2, in which the sample size was changed from 120 to 100 children. This change was approved by the Research Grants Council on May 17, 2022.

### Study Design

This is a comparative accuracy study that will compare the diagnostic accuracy of the MPT, SRT, and TST in children with and without CAS.

### Participants

A total of 25 children with CAS will be recruited for the study. The inclusion criteria are as follows: (1) age between 3 years and 6 years 11 months, (2) diagnosed with or suspected of having CAS by a qualified speech-language pathologist, (3) no hearing impairment or structural abnormality that affects speech production, and (4) Cantonese as the main language for daily communication. The same number of age- and gender-matched children will be recruited for each of the following 3 control groups: non-CAS SSDs only, non-CAS SSDs co-occurring with S&LI, and TD. The non-CAS SSD group will be recruited because it will allow a direct comparison between children with and without CAS. Research has shown that LI is usually present in children with CAS [5]; therefore, an S&LI group will be included to compare the performance of children with and without CAS, while controlling for language skills. A total of 100 participants will be recruited. Originally, a sample size of 172 participants (ie, 43 for each group) was estimated from the effect size of tone accuracy in a pilot study [20] via power analysis. An actual power of 0.954 could be achieved from 172 participants with an error probability of 0.05 (*F*_168_=2.658). There should be sufficient children with CAS in this population. However, taking into consideration the time and effort needed to screen and find suitable participants with and without CAS, SSD, and S&LI, it will be very challenging to recruit 172 participants within 2 years (the proposed study period). In addition, many reported studies [22,23] have only recruited 20 to 30 children with CAS for the investigations of assessment and diagnostic accuracy. Therefore, the total sample size was reduced to 100 participants.

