### Statistical Methods

For the statistical analysis, linear mixed-effects models will be used. Our models will include group (CAS vs SSD vs S&LI vs TD) as a fixed effect and participants and items as random effects.

The sensitivity and specificity of the MPT, SRT, and TST in making a diagnosis of CAS in Cantonese-speaking children will be determined using the receiver operating characteristics curve [40]. The new cutoff scores of the MPT and SRT to diagnose CAS in Cantonese-speaking children will be compared with the existing cutoff scores recommended for English-speaking children. The cutoff scores for the TST will also be determined from the receiver operating characteristics curve.

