## Results

Data collection started in January 2022 but was soon disrupted by the fifth wave of the COVID-19 pandemic in Hong Kong. As of August 2022, the project has recruited 4 children in the CAS group, 21 children in the non-CAS SSD group, 4 children in the S&LI group, and 53 children in the TD group. Data collection is ongoing and will continue until October 2023.

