This study faces several challenges. First, data collection started in January 2022 but was disrupted owing to the fifth wave of the COVID-19 pandemic in Hong Kong. Restrictions on face-to-face interactions during the fifth wave forced the cessation of data collection for several months. Although the fifth wave is now over, the parents of participants are still concerned about mask-off activities during data collection, resulting in slow progress in data collection. Second, the study is recruiting either patients with CAS with an existing CAS diagnosis or individuals suspected of having CAS by a qualified speech-language pathologist. However, a recent study has shown that about half of the Hong Kong speech-language pathologist respondents to a questionnaire (36/77, 47%) had never worked with children with CAS or suspected CAS. Furthermore, a majority of the respondents (64/77, 83%) rated their understanding of Cantonese CAS as “a little” or “fair” [43]. This may be because of a possible low prevalence of CAS in Hong Kong or limited understanding of CAS among local clinicians. Both factors could have limited participant recruitment in this study. In an effort to solve these problems, the research team has provided continuing education opportunities for local speech-language pathologists to enhance their understanding of CAS among Cantonese speakers. In addition, the research team may extend participant recruitment to Macau, another special administrative region of China, because, as in Hong Kong, the people of Macau also use Cantonese as their primary language for oral communication. Third, coexisting developmental issues in the participants may limit the results of this study. Owing to the challenge of recruiting participants with CAS, the research team will not control for coexisting developmental conditions in the participants, such as intellectual disability and ASDs, which may affect the speech production skills of the participants. The research team is aware of this limitation and will balance the sample size and coexisting developmental conditions of the participants.

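### Controls are to be age- and gender-matched over ages 3;0 to 6;11, but the stated model and ROC analysis contain no age, sex or matched-set term, and no rule says how 25 typically developing controls will be drawn from the 53 already enrolled

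*Protocol article*

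**What the plan says.** Protocol article, Participants: "A total of 25 children with CAS will be recruited for the study", with eligibility at "age between 3 years and 6 years 11 months". For the controls, "The same number of age- and gender-matched children will be recruited for each of the following 3 control groups" (non-CAS speech sound disorder, SSD; SSD with language impairment, S&LI; and TD). The size is then fixed: "A total of 100 participants will be recruited". No matching ratio, age tolerance or pairing procedure is given.

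Statistical Methods names the linear mixed-effects models and their terms: "Our models will include group (CAS vs SSD vs S&LI vs TD) as a fixed effect and participants and items as random effects". Sensitivity and specificity "will be determined using the receiver operating characteristics curve", with new cutoffs derived from it. Neither analysis mentions age, sex or the matched set.

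Results (and the Abstract) report that by August 2022 "the project has recruited 4 children in the CAS group, 21 children in the non-CAS SSD group", with 4 in the S&LI group and 53 in the TD group. The Recruitment section describes finding controls by open invitation, through parent chat groups, the university clinic and nearby kindergartens, with no step that ties a control to a case.

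Strengths and Limitations adds that "the research team will not control for coexisting developmental conditions in the participants", naming intellectual disability and autism spectrum disorder (ASD) as examples.

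**The concern.** Matching on two variables is a design commitment, and an analysis normally carries those variables. Here the model's terms are listed and they are absent. Two different problems follow, depending on whether matching works.

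- If the groups end up balanced on age, the group difference is not confounded by age. Age-related variation then sits in the error term: the standard error is too large and power is lost. That matters because the total was cut from 172 to 100 on feasibility grounds.
- If the groups are not balanced, any relation between age and score passes into the group difference and the ROC curve.

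The enrolment counts raise a linked question. TD enrolment is already more than double its target while the case group is nearly empty. Someone must decide which TD children enter the analysis. If that choice is made after scores exist, the control set could be chosen with knowledge of the results.

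**Working it through.** **1. The plan's own figure.** For a one-way comparison of 4 groups with N = 172 and alpha 0.05, critical F(3, 168) = 2.658, as stated. The effect size f is not given. Solving for stated power 0.954 gives f = 0.323 (noncentrality 172 × 0.323² = 17.9). With the same f, N = 100 gives power 0.76. This calculation treats the four groups as independent, with no matching and no covariate.

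**2. Enrolment counts.**
- Enrolled: 4 + 21 + 4 + 53 = 82.
- TD above plan: 53 − 25 = 28.
- TD children who could not be paired 1:1 with an enrolled case: at least 53 − 4 = 49.
- Still needed in the other groups: 21 CAS + 4 SSD + 21 S&LI = 46.
- Total if all TD are kept: 82 + 46 = 128. Reaching 100 means leaving out 28 TD children.

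**3. If matching succeeds.** The documents do not say how strongly age relates to scores, so a range is assumed. One value per child is used throughout.

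*Pairwise comparison, 25 vs 25, d = 0.61 (upper end of the pilot F0 effects), two-sided t test.* Adjusting for age multiplies the SE by √(1 − R²), so the effective d is 0.61/√(1 − R²).

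| Age R² | SE ratio | 25 per group acts like | Power |
|---|---|---|---|
| 0 (no adjustment) | 1 | 25 | 0.56 |
| 0.2 | 0.894 | 31 | 0.66 |
| 0.4 | 0.775 | 42 | 0.78 |

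*Four groups of 25 with identical ages, f = 0.323, by simulation.* With exact matching, the true SE of a group difference is √(1 − r²) of the one the model reports, where r is the correlation of age with score.

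| r | True SE / reported SE | Type I error, age out / in | Power, age out / in |
|---|---|---|---|
| 0.3 | 0.95 | 0.036 / 0.05 | 0.76 / 0.80 |
| 0.5 | 0.87 | 0.017 / 0.05 | 0.76 / 0.88 |
| 0.7 | 0.71 | 0.002 / 0.05 | 0.77 / 0.97 |

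The test without age is conservative.

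**4. If matching fails.** Ages 3;0 to 6;11 span 47 months. If ages are uniform (assumption), the SD is (47/12)/√12 = 1.13 years. Bias in SD units is r × gap / 1.13. For 25 vs 25 the SE is √(2/25) = 0.283, and the false-positive rate follows from the normal approximation.

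| r | 6-month gap: bias, false-positive rate | 12-month gap: bias, false-positive rate |
|---|---|---|
| 0.3 | 0.13 SD, 0.08 | 0.27 SD, 0.16 |
| 0.5 | 0.22 SD, 0.12 | 0.44 SD, 0.35 |
| 0.7 | 0.31 SD, 0.19 | 0.62 SD, 0.59 |

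The pilot effects in Previous Pilot Studies are d = 0.22–0.61 for F0, 0.9–1.45 for duration, 1.36–1.85 for consistency and 1.37–1.98 for tone accuracy. A 6-month gap is thus comparable with the smaller F0 effects and minor beside tone accuracy. The bias can inflate or mask a difference, depending on which group is older.

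**The case against.** The strongest reply is that a short article section is being read as a complete model. It says what the models will include, and Strengths and Limitations promises work on lexical status, syllable structure, number of syllables and syllable position, none of which appears among the listed terms. Covariates and ROC adjustment could sit in an analysis plan that is not shown. This stands in part: one cannot say that age will never be used. But the terms that are stated do not carry the matching that the same article makes a design feature.

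Several stronger readings are tempting and are not supported:

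- *Recruitment shows that matching has failed.* It does not. No ages or sexes are reported, enrolment was to run until October 2023, and matched controls could still be picked from the pool as cases arrive. The counts exclude 1:1 matching at entry for most TD children, and no more.
- *The analysis will suffer both age confounding and wrong standard errors.* These are alternatives. Balanced ages give oversized standard errors without confounding; unbalanced ages give bias.
- *Matching was planned because scores change with age.* The protocol gives no reason for matching and no figure for age dependence.
- *The remarks on coexisting conditions contradict each other.* The article says they will not be controlled and then speaks of balancing them with sample size. That most naturally means a trade-off against recruitment, and the limitation is openly declared.

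It is also fair that the bias looks large only beside the F0 effects; tone accuracy, which drove the sample size, is little threatened.

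**Conclusion.** The point holds in a limited form. The stated model and ROC analysis do not use the variables on which the groups are to be matched, and the enrolment figures do not fit equal groups of 25 and a total of 100 without a selection rule that the article does not give.

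The consequence depends on matching. If it succeeds, the cost is efficiency: pairwise power of 0.56 where 0.66–0.78 was available (d = 0.61, age R² 0.2–0.4), with conservative tests. If it fails, differences are biased by 0.13–0.31 SD for a 6-month gap (r 0.3–0.7), which is material for F0, and ROC results are affected too. The strength of the age relation, the gap and the uniform age distribution are all assumptions. No harm from omitting sex has been quantified; it belongs in the model because it is a matching variable. This is a change that should be made, not a defect that invalidates the study.

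**What to change.** 1. Add age in months and sex as fixed effects in every mixed model, and a matched-set term if children are matched individually. Report age-adjusted ROC results alongside the raw ones.
2. State how matching is done, and settle the TD group now. Either keep all enrolled TD children in the adjusted models and restate the expected total as 128, or fix a selection rule that uses only age and sex and is applied blind to MPT, SRT and TST scores.
3. Optional and secondary: a sensitivity analysis excluding children with identified ASD. One for intellectual disability is possible only where that diagnosis is recorded, since the Initial Assessment lists no cognitive test.

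The cost is wording and a few model degrees of freedom; age and sex must already be held in order to match. Restating the total as 128 also departs from the 100 that the funder approved (Protocol Version) and would need to be reported as a change. The selection rule avoids that.

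### The 172-child calculation (power 0.954) does not follow from the pilot effect named as its source, and no power is stated for the 100 children to be enrolled

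*Protocol article*

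**What the plan says.** The Participants section (Methods) gives "a sample size of 172 participants (ie, 43 for each group" as the original target and says that it "was estimated from the effect size of tone accuracy in a pilot study [20] via power analysis". The result is stated as "An actual power of 0.954 could be achieved from 172 participants with an error probability of 0.05", and the critical value follows in "error probability of 0.05 (*F*_168_=2.658". The effect size is not given as a number, and its metric is not named.

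The Previous Pilot Studies section (Introduction) describes the same pilot study, reference 20, and gives its tone-accuracy effect as Cohen d "ranging from 1.37 to 1.98".

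The Participants section then says that recruiting 172 within two years would be very hard and that other studies enrolled 20 to 30 children with CAS. It concludes: "Therefore, the total sample size was reduced to 100 participants". No power is given for 100. The Protocol Version section records the change to version 2 as 120 to 100 children, approved by the funder, and does not link 120 to 172.

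**The concern.** A d between 1.37 and 1.98 is very large. A four-group comparison planned on it should need far fewer than 172 children for 95% power. Either the 172 came from a smaller effect than the one reported, or the source is misdescribed.

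The choice matters because it decides how the cut to 100 should be read. With the reported effect, 100 children are ample for the omnibus test. With the effect that produces 172, the type II error rises from about 5% to about 24%. The article gives the reader no means of choosing between these, and its single power figure belongs to a design that has been given up.

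**Working it through.** **Inputs.** Participants section: N = 172, four groups of 43, alpha 0.05, power 0.954, critical F 2.658 with 168 denominator df; current N = 100 (25 per group). Protocol Version section: version 1 size 120. Previous Pilot Studies section: tone accuracy d = 1.37 to 1.98 for reference 20, and d = 0.68 for the initial version of the task in an earlier pilot.

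**Method.** One-way fixed-effects ANOVA, k = 4 equal groups, df (3, N − 4). Power = P(F′ > F crit), where F′ is noncentral F with λ = N·f².

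**1. The plan's own frame reproduces.** 172 − 4 = 168, and F(0.95; 3, 168) = 2.6584, which matches 2.658. The test is therefore the four-group omnibus F.

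**2. Effect implied by 0.954 at N = 172.** Solving for f gives 0.3229 (0.3225 to 0.3233 allowing for rounding of 0.954), so λ = 172 × 0.3229² = 17.9. At this f, N = 168 gives 0.949, so 172 is the smallest equal-group total that reaches 0.95. The calculation is coherent in itself.

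**3. That effect as a largest pairwise d.** The conversion depends on the pattern of the four means:
- two groups at each extreme: d = 2f = 0.65
- CAS differs from three equal control groups: d = 4f/√3 = 0.75
- two groups at the extremes, two midway (smallest possible f for a given d): d = f√8 = 0.91

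All three lie below 1.37.

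**4. The reported tone-accuracy effect run forward.**

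| d | pattern | f | N for 95% power | power at 172 | power at 100 |
|---|---|---|---|---|---|
| 1.37 | d/√8 | 0.484 | 80 | 0.9999 | 0.987 |
| 1.37 | d√3/4 | 0.593 | 56 | >0.999 | 0.9994 |
| 1.37 | d/2 | 0.685 | 44 | >0.999 | >0.999 |
| 1.98 | d/√8 | 0.700 | 40 | >0.999 | >0.999 |
| 1.98 | d√3/4 | 0.857 | 28 | >0.999 | >0.999 |
| 1.98 | d/2 | 0.990 | 24 | >0.999 | >0.999 |

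The first row is the least favourable arrangement possible at the bottom of the reported range, and it still needs only 80 children.

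**5. Could the earlier pilot be the source?** With d = 0.68, f = 0.340, 0.294 or 0.240 gives N = 156, 204 or 304. At f = 0.340 the power at 172 is 0.971. None gives 172 with 0.954.

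**6. Power of the current design at the implied effect.** With f = 0.3229:
- N = 120: λ = 12.5, power 0.843
- N = 100: λ = 10.4, power 0.761 (0.760 to 0.763 over the rounding range)

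This step needs no conversion from d. Whatever the metric of the input, the stated 0.954 at 172 fixes λ, and λ scales with N.

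**The case against.** The strongest reply is that no arithmetic error is shown. Critical F, degrees of freedom, allocation and power agree with one another, and f = 0.323 is a reconstruction that the article never states. The authors may have used an overall group effect from the pilot study (f = 0.323 is an eta-squared of 0.094) or a subset of its data; the Introduction's wording can be read as limiting the reported d values to word stimuli. A cautious planning value would also be reasonable, since that pilot study had 4 children with CAS and 3 in each comparison group. All of this stands. It means that the fault lies in the link between the calculation and its stated source, not in the calculation. It does not remove the fault, because the article names a source and elsewhere gives an effect for that source that does not lead to 172.

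The reply also rightly notes that the section calls 172 the original figure, says openly that N was cut and why, and never claims 0.954 for 100.

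Stronger readings that a reader might infer are not supported:
- **That 100 children are too few.** This holds only at the back-solved effect. At d = 1.37 the omnibus power is about 0.987 or more.
- **That F0 comparisons have only 12% to 56% power.** A t-test of 25 against 25 gives this range if the reported F0 effects, d "ranging from 0.22 to 0.61", are differences between child means. They evidently are not. With 4 children against 9, t = d√(4·9/13) is 0.37 to 1.02 (p = 0.72 to 0.33), yet the article calls those differences significant. The planned analysis is also a mixed model over repeated items. There is thus no basis for ruling in advance that a null F0 result is inconclusive.
- **That CAS must be shown poorer than each control group.** The hypothesis speaks of the control groups collectively, and a four-level group effect fits an omnibus calculation.
- **That sensitivity will be too imprecise with 25 children with CAS.** An interval would need an assumed result that the article does not give, and a precision statement may sit in a fuller document.

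**Conclusion.** The sample-size basis is wrong as written. Power 0.954 at 172 requires f of about 0.323 (largest pairwise d 0.65 to 0.91), while the named source is reported with d 1.37 to 1.98 (f at least 0.484), for which 80 children at most would give 95% power. The article states no power for the design being run. At the implied effect it is about 0.76 for 100 children, and was about 0.84 for the 120 of version 1; at the reported effect it is about 0.987 or more.

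This rests on the four-group one-way F test, which the critical value identifies, and on standard conversions between d and f for equal groups. It does not establish which effect is true, that the original calculation was miscomputed, or what power the mixed model will have. The mismatch and the power at 100 given 0.954 at 172 are firm; the reason for the mismatch cannot be settled without the pilot report.

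**What to change.** Revise the sample-size text in the Participants section to:
- state the effect value and metric behind 172 and where exactly they come from (which measure, which stimuli, which contrast, or a deliberately reduced planning value);
- reconcile that value with the d of 1.37 to 1.98 in Previous Pilot Studies;
- replace the 0.954 statement with the omnibus power of the 100-child design at that effect, which is about 0.76 if f is about 0.32;
- say that this figure is an ANOVA benchmark and not the power of the planned linear mixed-effects model.

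The cost is text only. No children, assessments or analyses are added. If f of about 0.32 is confirmed, the stated power becomes less favourable.
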